### Study procedures

2.2

Study blood handling will follow a standard operating procedure. Approximately 20 mL of venous blood will be withdrawn and collected. This will encompass a whole blood sample (4 mL) collected in PaxGene DNA tubes for DNA extraction and genotyping of ET_A_ SNPs, a second whole blood sample collected in PaxGene RNA tubes (2.5 mL) for quantification of ET_A_ mRNA and a 5 mL plasma sample for measurement of plasma endothelin related peptides. Blood will be centrifuged at 1500g for 20 mins at 4 °C. Plasma will be siphoned, aliquoted and stored at −80° ± 10°.

The PRIZE trial baseline clinical assessment includes patient interview, angina, quality of life and treatment satisfaction questionnaires, and Bruce protocol treadmill exercise testing (a full list of baseline assessments is provided in appendix B). These will be repeated at subsequent trial visits only if there have been significant changes in clinical status from initial screening otherwise results from these assessments will be used in the sub-study analyses.

SNP genotyping will be undertaken using the UK Biobank Axiom^TM^ Array. ET_A_ mRNA will be quantified in leucocytes and platelets within the samples using quantitative real-time polymerase chain reaction (qPCR). Big ET-1 and ET-1 will be measured by enzyme-linked immunosorbent (ELISA) immunoassay.

### Additional participant analyses

2.3

If valid consent for the sub-study procedures is available for participants recruited to PRIZE from sites outside of Cambridge, they are found to be eligible, and surplus stored frozen samples are available, these will be similarly analysed.

### MRI analysis for quantification of microvascular dysfunction

2.4

We will analyse enrolled patients' standard of care perfusion MRI prior to genetic analysis. Stress myocardial perfusion will be quantified globally, and as an endocardial to epicardial perfusion ratio. Where rest perfusion has been performed, MPR will be calculated.

## Statistical consideration

3

For sample size calculation, we considered a difference of 1.0 mL·g^−1^·min^−1^ for stress MBF on CMR clinically significant with a pooled standard deviation of 0.56 based on previous published data [14]. Additionally, based on pilot data from our laboratory, we have assumed a difference in circulating plasma ET-1 between patient groups of 0.4 pg/ml with a pooled standard deviation of 0.36 to be clinically meaningful. Power calculations for an independent samples *t*-test demonstrate that a sample size of 60 (estimated to give 51 patients with the risk associated rs1878406-C allele) will have > 80% power to detect significant differences in both stress MBF and in plasma ET-1 between patient genotypes with a level of significance of 0.05 for an alpha error (SPSS, IBM Corp., USA).

Normality of continuous variable distributions will be assessed using the one sample Kolmogorov-Smirnov Test. Continuous variables will be summarised as mean ± standard deviation if normally distributed and median (Inter-Quartile Range) if non-normally distributed. Appropriate paired difference tests will be used to compare continuous variables according to the normality of the distribution. The primary outcome measure will be the difference in the circulating concentrations of ET-1 related peptides and ET_A_ mRNA between observed genotypes. Secondary outcome measures will be exploratory, including differences in disease burden measured by questionnaires, exercise tolerance tests and perfusion CMR between various ET_A_ SNP genotypes. Clinical trials unit and data management support and storage will be via the use of OpenClinica.

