**Fig. 2 f0010:**
[figure not shown]
Phenome wide associations for rs6842241 with disease traits identified from the UK Biobank[30]. Traits (blue dots) above the red dotted line have a p value for association of < 1 × e^-8^. Chronic Ischemic Heart Disease (labelled) shows the strongest association. (For interpretation of the references to colour in this figure legend, the reader is referred to the web version of this article.)

The rs1878406 SNP is located 8.5 kb upstream from the EDNRA gene on chromosome 4. The major rs1878406-C allele occurs with a frequency of 85% in Caucasian populations and is associated with cardiovascular risk, whereas the T allele is protective [27], [28]. The rs6842241 SNP is located 1.25 kb upstream from the EDNRA gene within the regulatory region. The risk allele (G) of rs6842241 has a frequency of 83% and is highly correlated (r^2^ > 0.8) with both rs1878406 and another SNP, rs6841581 located further upstream [29], which has been been identified in functional analysis as a possible epigenetic regulator of EDNRA gene expression [29].

We hypothesise that in a microvascular angina population, these SNPs related to the ET_A_ receptor, will result in greater ET_A_ receptor activation, reduced myocardial perfusion and more angina. Additionally, we wish to investigate whether higher ET_A_ receptor expression is associated with more severe disease, even amongst those without elevated circulating ET-1 levels.

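### The sample-size paragraph uses the 85% C-allele frequency as a share of patients, so its implied 51:9 split fits no genotype contrast and the stated power does not hold for patients with versus without the allele

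*Protocol article*

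**What the plan says.** Section 1.3 of the protocol article (text after Fig. 2) describes the SNP: "The major rs1878406-C allele occurs with a frequency of 85% in Caucasian populations". It gives 83% for the risk allele of the correlated SNP rs6842241.

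Section 3 (Statistical consideration) sets the assumptions for an independent-samples t-test at alpha 0.05:

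- Stress MBF: a difference of 1.0 mL/g/min, with "stress MBF on CMR clinically significant with a pooled standard deviation of 0.56".
- Plasma ET-1: "a difference in circulating plasma ET-1 between patient groups of 0.4 pg/ml with a pooled standard deviation of 0.36".
- Group sizes: "a sample size of 60 (estimated to give 51 patients with the risk associated rs1878406-C allele".
- Conclusion: the study "will have > 80% power to detect significant differences in both stress MBF and in plasma ET-1 between patient genotypes".

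The same section makes ET-1 related peptides part of the primary outcome, compared across the genotypes observed. It does not say how the three genotypes are grouped for a two-sample test.

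**The concern.** The product 60 × 0.85 is exactly 51, and the article offers no other source for that count. A frequency per chromosome has become a proportion of patients. With a common allele the two differ greatly, because a patient lacks C only if both copies are T. The parenthesis points to a comparison of patients with and without C, and that comparison would have almost no one on the without side.

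At stake is the article's only power statement. It covers an outcome in the primary set (ET-1) and one of the two SNPs to be analysed first. Depending on a grouping that the text does not name, the same 60 patients either give ample power for the stated differences or leave a comparator group of one or none. If the grouping is settled only once the genotype counts are known, the main comparison becomes data-driven.

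**Working it through.** **Inputs.** From section 3: N = 60; ET-1 difference 0.4, SD 0.36; MBF difference 1.0, SD 0.56; alpha 0.05. Sidedness is not stated; two-sided is assumed. From section 1.3: C-allele frequency p = 0.85, so q = 0.15. Assumptions added here: Hardy-Weinberg proportions, and that the quoted population frequency applies to this cohort.

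**Formula.** Standardised difference d = difference / SD: ET-1 0.4/0.36 = 1.11; MBF 1.0/0.56 = 1.79. Power comes from the noncentral t distribution with 58 degrees of freedom, critical value 2.002 and noncentrality d × √(n1·n2/60).

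**1. The plan's own figure.** Subtraction gives 60 − 51 = 9. √(51·9/60) = 2.766, so the noncentrality is 3.07 for ET-1 and 4.94 for MBF. Power is 85.6% and 99.8%. The claim of more than 80% reproduces at 51:9.

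**2. Expected genotype counts.**
- CC: 60 × 0.85² = 43.35
- CT: 60 × 2 × 0.85 × 0.15 = 15.30
- TT: 60 × 0.15² = 1.35
- At least one C: 43.35 + 15.30 = 58.65, not 51
- No C: 1.35, not 9

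For 85% of patients to carry C, the allele frequency would have to be 1 − √0.15 = 0.61. For 85% to be CC, it would have to be √0.85 = 0.92. Neither agrees with section 1.3.

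**3. Power for each possible split.**

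| Split | ET-1 | Stress MBF |
|---|---|---|
| 51:9 (as printed) | 85.6% | 99.8% |
| 59:1 (C carriers v TT) | 19% | 41% |
| 58:2 (C carriers v TT) | 33% | 68% |
| C carriers v TT, averaged over TT ~ Bin(60, 0.0225) | 22% | 44% |
| 43:17 (CC v T carriers, same differences) | 96.8% | >99.9% |

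The chance of no TT patient is 0.9775⁶⁰ = 26%, and of at most one 61%. ET-1 needs at least 8 patients in the smaller group for 80% (52:8 gives 82%, 53:7 gives 78%). The chance of 8 or more TT patients in 60 is about 0.00006.

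**4. Sensitivity.**
- With 83%, the article's figure for rs6842241, expected TT is 60 × 0.17² = 1.73, and average power for carriers v non-carriers is 28% and 53%.
- One-sided testing at 58:2 gives 45% and 79%, still under 80%.
- An inbreeding coefficient of 0.1 raises expected TT only to 2.1. Nine would need a coefficient of 1, that is, no heterozygotes at all.

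**5. Detectable differences at 43:17.** Power of 80% needs d = 0.816: 0.816 × 0.36 = 0.29 pg/ml and 0.816 × 0.56 = 0.46 mL/g/min.

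**6. Why the 97% is conditional.** Suppose, for illustration only, that 0.4 pg/ml is the CC v TT difference and the effect is additive, at 0.2 per allele. T carriers have on average (15.30 + 2 × 1.35)/16.65 = 1.08 T alleles, so the CC v T-carrier difference is about 0.22 pg/ml. ET-1 power at 43:17 is then about 54%, and about 57% for a per-allele regression.

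**The case against.** The strongest reply is that section 3 claims power only between genotypes. The with-or-without-C contrast comes from a count in parentheses, and the comparator of 9 is never printed. Any split with at least 8 patients in the smaller group supports more than 80% power, including the 43:17 that CC v T carriers would give. This stands: a reader might infer that 60 patients are too few, and the article does not support that. The low power belongs to one contrast, which the text implies but does not define.

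A reader might also infer the opposite, that regrouping as CC v T carriers secures 97% power. That is not supported either. The 0.4 pg/ml comes from pilot data for unspecified patient groups, and nothing ties it to that contrast.

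Three further points carry some weight. A fuller protocol or analysis plan may define the coding; but the point here is a wrong printed count, not an omission. Stress MBF falls under the perfusion CMR outcomes, which section 3 treats as secondary and exploratory, so the ET-1 figures matter more. And N = 60 follows from expected re-consent among 66 screen failures (section 2.1), with possible extra samples from other sites (section 2.3), so the 51 does not drive recruitment. None of these corrects the sentence. The extra samples are conditional and unquantified, and about 291 patients would be needed for 80% ET-1 power in C carriers v TT.

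**Conclusion.** The group size is wrong as written, and the power claim resting on it cannot stand in its present form. The count of 51 is neither the expected number of C carriers (about 59) nor of CC homozygotes (about 43). For patients with v without C, power is about 19–33% for ET-1 and 41–68% for stress MBF (22% and 44% on average), not more than 80%. For CC v T carriers it is about 97% and over 99%, only if 0.4 pg/ml and 1.0 mL/g/min are differences for that contrast.

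The counts rest on Hardy-Weinberg proportions and on the quoted population frequency; moderate departures from either do not restore nine non-carriers. Whether N = 60 is adequate remains open until the contrast, and the difference that belongs to it, are stated.

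**What to change.** In section 3:

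1. Replace the 51 with the expected genotype counts: about 43 CC, 15 CT and 1 or 2 TT, with the Hardy-Weinberg assumption stated.
2. Name a contrast with a usable comparator, for example CC v T carriers, or a per-allele (0/1/2) model. The choice is the authors'.
3. State which contrast the 0.4 pg/ml and 1.0 mL/g/min differences refer to.
4. Restate power for that contrast. For CC v T carriers at 43:17, give about 97% (ET-1) and over 99% (MBF) as conditional on those differences, together with the differences detectable at 80% power: about 0.29 pg/ml and 0.46 mL/g/min. For a per-allele model, calculate power separately.
5. If a sensitivity value is wanted, use the article's own 83% for rs6842241.

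Cost: one rewritten paragraph, changed group sizes and a power figure that becomes conditional. Correcting the statement needs no extra patients.

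### The analysis sentence names paired tests, but every listed outcome compares unmatched patients in different genotype groups, and the sample size rests on an independent-samples t-test

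*Protocol article*

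**What the plan says.** All the relevant text is in the protocol article, section 3, Statistical consideration.

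- **Sample size.** "Power calculations for an independent samples *t*-test demonstrate that a sample size of 60" gives more than 80% power for stress myocardial blood flow (MBF) and for plasma ET-1, "between patient genotypes with a level of significance of 0.05". The group sizes come from the remark that 60 patients are "estimated to give 51 patients with the risk associated rs1878406-C allele".
- **Analysis rule.** After normality has been assessed, "Appropriate paired difference tests will be used to compare continuous variables according to the normality of the distribution". No other sentence in the article names the test for continuous outcomes.
- **Primary outcome.** It is "the difference in the circulating concentrations of ET-1 related peptides and ET_A_ mRNA between observed genotypes".
- **Secondary outcomes.** These are exploratory: differences in questionnaires, exercise tolerance and "perfusion CMR between various ET_A_ SNP genotypes".

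**The concern.** A paired t-test or a signed-rank test works on differences within linked pairs: the same patient measured twice, or two patients matched by design. A patient has only one genotype at a given SNP, so patients in different genotype groups are different people. The article describes no matching and no crossover, and none of its outcomes is a before-and-after comparison. The planned test therefore belongs to the wrong class for the primary outcome, and it differs from the test used to justify the sample size.

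At stake is the published rule for the primary analysis. An analyst who follows it has nothing to compute unless pairs are invented, and the p-value would then depend on which pairs were chosen. An analyst who sensibly runs an unpaired test departs from the published plan.

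**Working it through.** **Step 1. Look for any pairing in the design.**

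- Study procedures (2.2) describes one set of sub-study blood samples per patient. Clinical assessments are repeated only after a significant change in clinical status; otherwise the screening results are used. No planned before-and-after contrast follows from this.
- MRI analysis (2.4) yields some within-patient data: stress and rest perfusion, and endocardial and epicardial perfusion. Each of these pairs is reduced to a ratio for each patient, and section 3 then compares perfusion CMR between genotypes. No listed outcome tests the within-patient contrast itself.
- Section 3 expects 51 patients in one group, which leaves 60 − 51 = 9 in the other. Groups of 51 and 9 cannot be paired one to one.

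**Step 2. Reproduce the article's power with the test it names there.**

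Inputs, all from section 3: stress MBF difference 1.0 with SD 0.56; plasma ET-1 difference 0.4 pg/ml with SD 0.36; groups of 51 and 9; alpha 0.05. Sidedness is not stated, and two-sided is assumed.

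The noncentrality parameter is (difference / SD) / √(1/n₁ + 1/n₂), with n₁ + n₂ − 2 = 58 degrees of freedom. Here √(1/51 + 1/9) = 0.3616.

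| Outcome | Difference / SD | Noncentrality | Power (exact noncentral t) |
|---|---|---|---|
| Stress MBF | 1.0 / 0.56 = 1.786 | 4.94 | 99.8% |
| Plasma ET-1 | 0.4 / 0.36 = 1.111 | 3.07 | 85.6% |

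Both exceed 80%, so the stated figure reproduces as an unpaired calculation. With a rank-sum test in place of the t-test, ET-1 power would be about 84% (assumed asymptotic relative efficiency 0.955).

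**Step 3. Illustration only: what a literal reading would require.**

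At most 9 pairs could be formed, using 18 patients and discarding 60 − 18 = 42. The SD of a within-pair difference is SD × √(2(1 − ρ)), the noncentrality is (difference / SD of difference) × √9, and there are 8 degrees of freedom.

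| Outcome | Assumed ρ | SD of difference | Noncentrality | Power |
|---|---|---|---|---|
| Plasma ET-1 | 0 | 0.509 | 2.36 | 54.4% |
| Plasma ET-1 | 0.5 | 0.360 | 3.33 | 83.0% |
| Stress MBF | 0 | 0.792 | 3.79 | 91.1% |

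Unrelated patients paired arbitrarily correspond to ρ = 0. Nothing in the design supports ρ = 0.5; that row only shows how far the result depends on the assumption.

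**The case against.** The strongest reply is that this is a slip, for unpaired or for pairwise. The correct class of test is named in the preceding paragraph, the groups cannot be paired, and any competent analyst would be stopped by the shape of the data. A silently wrong result is therefore unlikely. This is fair, and it limits the consequences. It does not rescue the sentence, which is the article's only statement of how continuous outcomes are compared. The adjective at its head does not help either: it qualifies paired tests, and the choice it leaves open is tied to normality, that is, parametric or rank-based.

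A second reply is that a separate analysis plan may give the right test. That would answer a complaint of omission. Here the article states something positively, and it conflicts with the same section.

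A reader might also infer more than the documents support:

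- *That the power claim fails.* It does not. The calculation already uses the unpaired test and reproduces.
- *That the study stands to lose 42 patients or about 30 points of ET-1 power.* Arbitrary pairing is planned nowhere, and the figure depends on an assumed correlation.
- *That every comparison in the study is affected.* The finding covers every listed outcome. The sentence speaks of continuous variables in general, and some within-patient data exist, though no listed outcome tests them.

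Whether 51 to 9 is the right genotype split is a separate question. It needs assumptions about genotype proportions and grouping that the article does not state, and this point does not depend on it.

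**Conclusion.** The point holds as an internal contradiction. The analysis sentence names a class of test that has no defined input for any listed primary or secondary outcome, and it conflicts with the independent-samples calculation in the same section. The text must be corrected because it governs the primary analysis, but it is a wording correction. The sample size of 60 and the stated power stand, given the article's own effect sizes, SDs and 51 to 9 split and an assumed two-sided test. The conclusion that paired tests do not fit rests on the design alone and needs none of the power figures.

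**What to change.** Replace the sentence on paired tests with:

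> Between-genotype comparisons of continuous variables will use tests for independent groups: independent-samples t-test, or Mann-Whitney U if non-normal, for two genotype groups; one-way ANOVA or linear regression on genotype, or Kruskal-Wallis if non-normal, for three.

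Deleting one word would not be enough. A SNP with two alleles can produce three genotypes, and the outcomes refer to observed genotypes without fixing two groups, so the three-group case needs its own tests. For the primary outcome, the authors should also state before analysis whether genotype is coded as two groups or three, and which of the listed methods applies.

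The cost is one sentence in section 3. It needs no extra patients, samples or data and no new sample-size calculation.

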### Genetic dysregulation of Endothelin-1 and microvascular angina

1.3

The PRIZE trial is notable amongst cardiovascular clinical trials for defining eligibility by genetic analysis thus invoking a ‘precision medicine’ pathway whereby therapy will be targeted at those most likely to benefit. The genetic variant tested during screening for the PRIZE trial is the G allele of the rs9349379 SNP (single nucleotide polymorphism) found in the third intron of the PHACTR1 gene on chromosome 6. This variant has been linked to cardiovascular risk via enhanced Endothelin (EDN1) gene expression and is relatively common, with an estimated population frequency of 36% [23], [24]. In a sub-study of the British Heart Foundation Coronary Microvascular Angina (CorMicA) trial, patients with the rs9349379-G allele had significantly increased circulating concentrations of ET-1 as well as a higher likelihood of CMD, more myocardial perfusion defects on CMR, and decreased exercise tolerance when compared to patients without [25].

The principal aim of the PRIZE ET Sub-study is to identify additional novel, hitherto unknown functional genetic variants associated with microvascular angina, other than the rs9349379-G allele described above. For this reason, the study will run in parallel with the main PRIZE trial by preferential enrolment of the patients who are not selected after genetic screening for the rs9349379-G allele. Patient samples obtained in this parallel study will be genotyped using the UK Biobank Axiom^TM^ DNA Microarray. Briefly, the process involves extraction of DNA from whole blood, which is then denatured and fragmented, flourescentally labelled, and added to the array – a laborotary plate embedded with hundreds of thousands of DNA ‘probes’ (specific oligonucleotide sequences complementary to the genomic SNPs of interest). In the presence of a complementary DNA sequence, binding will occur by hybridization and scanning of the array for specific patterns of fluorescence can be used to identify genomic SNPs present in the patient's DNA [26]. In our study, analysis will be focused in the first instance, on SNPs located close to the gene encoding the ET_A_ receptor (EDNRA) with highly significant GWAS associations for ischemic heart disease, namely rs1878406 (Fig. 1) and rs6842241 (Fig. 2).

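### The tests named for the genotype comparison leave no place for ancestry, although the planned genome-wide array would allow adjustment for it

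*Protocol article*

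**What the plan says.** All from the protocol article.

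- **Test (section 3, Statistical consideration).** The article says that paired difference "tests will be used to compare continuous variables according to the normality of the distribution". No covariate or ancestry term is named.
- **Primary outcome (same section).** "The primary outcome measure will be the difference in the circulating concentrations of ET-1 related peptides" and ET_A "mRNA between observed genotypes".
- **Power (same section).** Based on an independent samples *t*-test. The calculations "demonstrate that a sample size of 60 (estimated to give 51 patients with the risk associated rs1878406-C allele) will have > 80% power" for stress MBF and plasma ET-1.
- **Allele frequency (section 1.3, text after Fig. 2).** "The major rs1878406-C allele occurs with a frequency of 85% in Caucasian populations". The 51 of 60 in the power statement equals this 85% applied to the whole sample.
- **Genotyping (sections 1.3 and 2.2).** Samples are to be typed on the UK Biobank Axiom array, a plate "embedded with hundreds of thousands of DNA" probes.
- **Who enters (sections 2.1 and 2.3).** Cambridge patients screened out of the main trial, plus eligible stored samples from other sites. The text shown sets no ancestry limit. The main trial's exclusion criteria are in appendix A, which is not shown.

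**The concern.** Genotype is observed, not assigned, so this is an association study. Ancestry is the familiar confounder in that setting: it can be related to allele frequency and, separately, to the outcome. A *t*-test or rank test between genotype groups cannot remove it.

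The article names a class of test and one criterion for choosing within it. That differs from naming a regression and leaving its covariates to a later document, because adding ancestry here would mean changing the stated method.

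At stake is whether a difference in ET-1 or ET_A mRNA can be read as an effect of variants near EDNRA. The article intends such findings to help identify further patient groups likely to benefit from the drug. The smaller genotype group is small on any count, so a few patients of another ancestry could move its mean.

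**Working it through.** **1. The plan's own power figure.** Inputs from Statistical consideration: ET-1 difference 0.4 pg/ml, SD 0.36; MBF difference 1.0, SD 0.56; groups 51 and 9; alpha 0.05, taken as two-sided.

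- Noncentrality = (difference/SD) / √(1/51 + 1/9), with 58 df.
- ET-1: 1.111 / 0.3616 = 3.07, power **85.6%**.
- MBF: 1.786 / 0.3616 = 4.94, power **99.8%**.

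Both agree with the stated figure of more than 80%. No figure in the plan is disputed here.

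**2. Spurious difference when the SNP has no effect.** Assumed, because the documents do not give them: share *w* of patients from a second ancestry, 5-20%; T frequency there 0.30-0.50, against 0.15 (1 − 0.85) in the main ancestry; outcome shift *D* between ancestries 0.5-1.0 SD. The contrast is CC v T carriers. With *a*₁ = 0.85² = 0.7225 and *a*₂ = (1 − T frequency)²:

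- Second-ancestry share among CC: *p*A = *w a*₂ / [(1 − *w*) *a*₁ + *w a*₂]
- Second-ancestry share among T carriers: *p*B = *w*(1 − *a*₂) / [(1 − *w*)(1 − *a*₁) + *w*(1 − *a*₂)]
- Spurious difference = (*p*B − *p*A) × *D*

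The error rates below come from simulating 60 patients, 10,000 replicates per row.

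| *w* | T freq. | *D* (SD) | *p*A | *p*B | Spurious diff. (SD) | Unadjusted error |
|---|---|---|---|---|---|---|
| 0.05 | 0.30 | 0.5 | 0.034 | 0.088 | 0.03 | 5.0% |
| 0.10 | 0.50 | 0.5 | 0.037 | 0.231 | 0.10 | 6.5% |
| 0.10 | 0.50 | 1.0 | 0.037 | 0.231 | 0.19 | 10.8% |
| 0.20 | 0.30 | 1.0 | 0.145 | 0.315 | 0.17 | 8.8% |
| 0.20 | 0.50 | 1.0 | 0.080 | 0.403 | 0.32 | 19.7% |

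Over all 12 combinations of *w* = 0.05, 0.10, 0.20, T frequency 0.30 or 0.50, and *D* = 0.5 or 1.0, the error is below 9% in ten. With ancestry in the model it is about 5% in every one. At *w* = 0 the difference is zero.

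On the ET-1 scale the largest value is 0.324 × 0.36 = 0.117 pg/ml, or 29% of the 0.4 pg/ml target (0.117/0.4).

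**3. Cost of adjustment, on the plan's 51 v 9 split.** With *k* covariates, df = 58 − *k*, and the noncentrality 3.07 is multiplied by √(1 − *k*/59). This allows for chance correlation of the covariates with genotype.

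| *k* | ET-1 power |
|---|---|
| 0 | 85.6% |
| 2 | 84.3% |
| 3 | 83.7% |
| 5 | 82.3% |
| 10 | 78.4% |

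Step 2 uses CC v T carriers, about 43 v 17 of 60 under Hardy-Weinberg proportions (60 × 0.7225 = 43.35). Step 3 keeps the plan's 51 v 9. Whether 85% should be applied to persons at all is a separate question.

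**The case against.** **The article is silent, not wrong.** It never says that the comparison will be unadjusted, and covariates are often left to a full protocol or SAP, which are not shown. The sentence on tests is general and comes before the primary outcome; the *t*-test is named only for power. This has weight, and a reader should not infer that adjustment was deliberately ruled out. Still, the only tests named for continuous variables have no place for a covariate, and both the peptides and the mRNA are continuous.

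**The sentence is miswritten anyway.** It calls the tests paired, which does not fit independent genotype groups and conflicts with the power calculation. That is a defect in its own right. It weakens the sentence as evidence of intent, but it also means that the sentence must be rewritten.

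**Nothing shows a mixed cohort.** This stands. The reference to Caucasian populations describes a cited allele frequency, not recruitment; most patients come from one centre; and appendix A might contain a restriction.

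**The larger error rates need extreme inputs.** This stands too. About 20% arises only when the highest assumed share, allele frequency and outcome shift occur together.

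**Adjustment is not free.** This is correct. Components that are truly related to genotype would cost more power than step 3 shows, and ten covariates would take ET-1 power below 80%.

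**Conclusion.** The point holds as a recommended improvement, not as a demonstrated bias. The tests named cannot account for ancestry, nothing in the text shown restricts it, and the planned array would provide the means to adjust. If the cohort is mixed, the spurious difference is about 0.03-0.32 SD and the type I error about 5-20%, mostly under 10%. Both ranges rest wholly on assumed shares, allele frequencies and outcome shifts. With a single ancestry the concern disappears.

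Two stronger readings are not supported. A reader might infer that the array data already exist; sections 1.3 and 2.2 describe genotyping still to be done, and samples from other sites are included only where consent, eligibility and stock allow. A reader might also infer that no primary difference could be attributed to the EDNRA variant. The documents give no ancestry figures to support that, and even the largest assumed bias is 29% of the ET-1 target.

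**What to change.** Rewrite the sentence on tests in Statistical consideration:

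- Make the primary genotype comparison a linear regression of each outcome on genotype, adjusted for the first two or three ancestry components derived from the array.
- Keep an independent-groups test, not a paired one, as a descriptive companion.

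Allele-count coding, a log scale for skewed outcomes, age and sex terms, and a European-ancestry subset analysis are optional. Age and sex do not address ancestry.

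Cost: no new sample or assay, and a little more analysis work. On the 51 v 9 split, ET-1 power goes from 85.6% to 84.3% with two components or 83.7% with three, and to 82.3% with five covariates. The stated 80% is kept on those assumptions; the covariate list should stay short.

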## Introduction:

1

Ischaemic heart disease is the leading cause of premature disability and death worldwide, with stable angina pectoris the commonest symptomatic manifestation, affecting 112 million people [1], [2], [3]. Angina pectoris occurs due to a relative myocardial oxygen supply–demand mismatch, typically during physiological (e.g. exercise) or psychological stress. Historical teaching placed a causal link between obstructive epicardial coronary artery disease and angina. However, in patients undergoing coronary angiography with evidence of myocardial ischemia, the prevalence of non-obstructive coronary disease is reported in up to 70% with higher frequencies among women [2]. Cardiac ischemia in the absence of significant epicardial coronary stenosis is termed INOCA (Ischemia and No Obstructive Coronary Artery Disease). This group of patients experience long-term adverse outcomes including recurrent angina, cardiovascular death and myocardial infarction (MI) as well as lower quality of life and health anxiety causing repeated presentations to healthcare services [4], [5], [6], [7]. High quality trial data for drug therapy in this condition is lacking and standard anti-anginal therapy is unsatisfactory for many patients [2]. Based on previous studies of INOCA populations (typically excluding those whose ischemia is attributable to non-coronary cardiac or systemic diseases such as hypertrophic cardiomyopathy and valvular heart disease), it is estimated that in around two-thirds, coronary microvascular dysfunction (CMD) represents the underlying pathology [8], [9]. Microvascular angina is the name given for the clinical syndrome caused by CMD in these patients. The Coronary Vasomotion Disorders International Study (COVADIS) group have recently defined the diagnostic criteria for microvascular angina (Table 1) [10]. This definition of microvascular angina aligns with the term 'type 1 CMD' described initially by Camici and Crea [11]. The other principal INOCA endotype is epicardial vasospastic angina (VSA) which may co-exist with microvascular angina in some patients.

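### Comparing genotype groups with a prespecified linear model including age and sex would be a cheap improvement on the unadjusted two-group tests

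*Protocol article*

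**What the plan says.** Section 3 (Statistical consideration) describes how continuous variables are compared between genotypes. Normality is assessed first, and difference tests "will be used to compare continuous variables according to the normality of the distribution". The sample size rests on "Power calculations for an independent samples" t-test, "with a level of significance of 0.05 for an alpha error". From this the article concludes that 60 patients "will have > 80% power to detect significant differences in both stress MBF and in plasma ET-1 between patient genotypes".

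The primary outcome is the difference between genotypes in ET-1 related peptides and ET_A mRNA. Questionnaires, exercise tolerance and perfusion CMR are secondary and labelled exploratory.

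No regression model or covariate is named anywhere in the article. On the data available, section 2.2 (Study procedures) says "The PRIZE trial baseline clinical assessment includes patient interview" along with questionnaires and a treadmill test. Age and sex are not listed by name there, but they can be taken as known for every enrolled patient.

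**The concern.** A t-test, or the rank test that would replace it for a skewed outcome, has no place for a covariate. The genotype groups are observed, not randomised or stratified, and by the plan's own count one of them holds 9 patients. This has two consequences.

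- Variation in ET-1, mRNA, perfusion or treadmill time that age and sex could explain is left in the residual variance, which widens the confidence interval for the genotype difference.
- If the small group happens to be older, or to contain more women, that imbalance goes straight into the estimate.

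Genotype cannot cause age or sex, so adjusting for them does not remove part of the genotype effect. What is at stake is precision in a small study, above all for the primary ET-1 and mRNA comparisons.

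**Working it through.** **Inputs from section 3.** ET-1: difference 0.4 pg/ml, pooled SD 0.36. Stress MBF: "we considered a difference of 1.0" mL/g/min, "for stress MBF on CMR clinically significant with a pooled standard deviation of 0.56". Total 60, with 51 in the C-allele group, leaving 60 − 51 = 9. Alpha 0.05.

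**Assumptions.** The test is two-sided (not stated). R-squared is the share of within-genotype variance explained by age and sex together. The article gives no value, so 0 to 0.30 is used. For the imbalance calculations, 60% of patients are women.

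**Step 1: reproduce the plan's power (noncentral t, 58 df).**

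Noncentrality = difference / (SD × √(1/51 + 1/9)), where √(1/51 + 1/9) = 0.3616.

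- ET-1: SE = 0.36 × 0.3616 = 0.130; noncentrality = 0.4/0.130 = 3.07; power 85.6%.
- Stress MBF: SE = 0.56 × 0.3616 = 0.2025; noncentrality = 1.0/0.2025 = 4.94; power 99.8%.

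Both exceed 80%, as the article claims, without any adjustment.

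**Step 2: cost of adjustment.** Two covariates reduce the degrees of freedom from 58 to 56. Chance correlation between genotype and the covariates also inflates the variance of the genotype difference. Simulating one continuous and one binary covariate at 51 and 9 gives a mean factor of about 1.037.

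**Step 3: ET-1 power after adjustment.** The SE is multiplied by √(1.037 × (1 − R²)).

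| Assumed R² | SE ratio, adjusted to unadjusted | ET-1 power |
|---|---|---|
| unadjusted | 1 | 85.6% |
| 0 | 1.018 | 84.3% |
| 0.02 | 1.008 | 85.0% |
| 0.05 | 0.993 | 86.1% |
| 0.10 | 0.966 | 87.8% |
| 0.20 | 0.911 | 91.2% |
| 0.30 | 0.852 | 94.3% |

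Adjusted and unadjusted power are equal at R-squared of about 0.037. The largest loss is 85.6 − 84.3 = 1.3 points; the gain at R-squared 0.30 is 94.3 − 85.6 = 8.7 points.

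**Step 4: how often imbalance arises.** By the normal approximation, the SE of the difference in the proportion of women is √(0.6 × 0.4 × (1/51 + 1/9)) = 0.177. A difference above 20 percentage points in either direction is 0.20/0.177 = 1.13 SEs, so it occurs in about 26% of cohorts. With a group of 9 this is only approximate.

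**The case against.** The strongest case against is that nothing here is stated wrongly. The article is condensed, an unseen analysis plan may name covariates, and the secondary outcomes are exploratory. That is fair as to severity. The article does, however, commit to a class of test that cannot take covariates, so the point concerns a stated choice and not a gap.

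Three stronger readings are tempting and are not supported.

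- *Adjustment is free.* A reader might infer this by counting only the two degrees of freedom. Once chance imbalance is included, adjustment loses a little power below R-squared of about 0.04, and nothing in the article shows that plasma ET-1 exceeds that value. The introduction's remark "with higher frequencies among women" is about how common non-obstructive disease is, not about variance in any outcome here.
- *The study is underpowered without adjustment.* It is not, on the plan's own figures: the claim of more than 80% reproduces for both outcomes.
- *The sample is fixed at 60, so this is the only route to precision.* Section 2.3 allows stored samples from other sites to be analysed as well.

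The gain for exercise time is also uncertain. Section 2.1 admits some patients because they exceeded the main trial's exercise limit, so the cohort is partly selected on that outcome.

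Two other matters in section 3 are separate and more pressing. The tests are called paired although the genotype groups are different patients. The count of 51 applies an 85% allele frequency to patients. If the groups were instead CC against T carriers, about 43 and 17 under Hardy-Weinberg proportions (assumed; 60 × 0.85² = 43.35), unadjusted ET-1 power would already be 96.8%, leaving little to gain in power.

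**Conclusion.** The point holds as a cheap improvement, not as an error in the plan. For ET-1 at 51 and 9, adjustment changes power by between −1.3 and +8.7 points, and the standard error by between about +2% and −15%, as R-squared runs from 0 to 0.30. It also takes chance age and sex imbalance out of the estimate, to the extent that a linear model captures their effects. The gain for stress MBF is negligible because power is already 99.8%. The size rests on an assumed R-squared, a two-sided test, 60% women, the plan's own split, and a simulated average imbalance cost. The balance favours adjustment because the possible loss is small and bounded, while the possible gain is several times larger.

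**What to change.** In section 3, make the main analysis of ET-1, Big ET-1, ET_A mRNA, stress MBF and exercise time a prespecified linear model with genotype, age (continuous) and sex, on the log scale where the outcome is skewed. Keep the unadjusted comparison between independent groups as a sensitivity analysis. The sentence on difference tests needs rewriting anyway because of the word paired, so the change can be made there.

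The cost is one sentence, two degrees of freedom, and at worst about 1.3 points of ET-1 power. No new data, visits or patients are needed.
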